**Figure 1 F1:**
[figure not shown]
Flow chart of study protocol. VAS, Visual Analogue Scale; SF-36, 36-Item Short Form Health Survey.

Predischarge, and 1 week, 1 and 3 months, 1 and 2 years after surgery: pain, wound infection, haematoma and seroma in the inguinal region and hernia recurrence will be recorded. Medical costs during hospitalisation and patient quality of life after discharge will be also recorded. The flow chart of study protocol is shown in figure 1. And The Standard Protocol Items: Recommendations for Interventional trials (SPIRIT checklist (Standard Protocol Items: Recommendations for Interventional Trials)) was followed in designing the study protocol (see online supplementary file 2).

10.1136/bmjopen-2017-016481.supp2Supplementary file 2

### Inclusion criteria

Male patients presenting with all of the following conditions will be considered for study admission:Diagnosed with primary unilateral inguinal herniaAged 18–80 yearsAmerican Society of Anesthesiologists (ASA) classification I–IIProvision of informed consent

### Exclusion criteria

Patients with any one or more of the following will be excluded from this study:Severe organ dysfunction or inability to tolerate surgeryHernia recurrenceGiant hernia (inner size of the hernia >4 cm)Scrotal herniaIncarcerated inguinal herniaInability to complete follow-up or questionnaire because of mental disorder or other reasonsHistory of preperitoneal surgery, such as radical prostatectomy

### Randomisation and blinding

This study is a multicentre trial, so stratified block randomisation will be performed in each centre. A randomisation sequence table will be generated by a statician who will not be involved in the trial using Statistical Analysis System (SAS V.9.1). The serial numbers assigned to each patient will be preserved in opaque sealed envelopes. The sealed envelopes will be subsequently given to the trial centre. All patients will not know the surgical regimen until after the surgery. The surgeons will not be blinded to the surgical regimen. Outcome assessors will be blinded to the surgical records in the electronic case report form (eCRF).

### Interventions

Based on recommendations for treatment and follow-up of inguinal hernias in adults made by the Chinese Medical Association and Chinese Medical Doctor Association^17^ and the European Hernia Society.^18^

#### Anterior transversalis fascia repair

An oblique skin incision will be made parallel to the inguinal groove from the inner to the outer inguinal ring. Subcutaneous tissue will be dissected until the external oblique aponeurosis is reached. Haemostasis will be achieved by electric coagulation. A4–6 cm long skin incision will be made on the external oblique aponeurosis, starting from the pubic tubercle, to fully expose the pubic tubercle and the inner ring.

The lower part of the external oblique aponeurosis will be separated from the spermatic cord. The upper part of the external oblique aponeurosis will then be separated from the internal oblique aponeurosis and dissociated to a point 3 cm above the inguinal canal wall. The overlying spermatic cord and cremaster muscle will be lifted up and disassociated about 2 cm above the pubic tubercle. The ilioinguinal nerve, external spermatic vessels and genital nerves concomitant with the spermatic cord will be protected while the spermatic cord is lifted.

The inguinal canal will then be dissected and the hernia sac will be dissociated from the surrounding tissue. The cremaster muscle fibres will be separated longitudinally and the hernia sac will be separated from the spermatic cord. The hernia sac will be dissociated until the neck of the hernia sac is reached. All abdominal contents in the hernia sac will be returned to the abdominal cavity. In cases with a small hernia sac, the sac will also be returned to the anterior peritoneal cavity to minimise postoperative pain. In cases with a large hernia sac, the distal end will be transected and opened, and the proximal part will be ligated at a high position.

A patch designed with an arc-shaped head and a swallow tail-like end that comprises two pieces (a wide top piece and a narrow bottom piece) will be sutured and fixed with non-absorbable polypropylene sutures. The inner side of the patch will be sutured to the pubic tubercle and the lateral boundary of the rectus abdominis muscle. The upper border of the patch will be sutured to the conjoined tendon and its border with the inguinal ligament and iliopubic tract. The wound will then be closed using layered sutures according to anatomic position.

#### Preperitoneal space repair

The skin will be cut and subcutaneous tissue will be dissected. The abdominal external oblique aponeurosis will be dissected along the fibres. The abdominal internal oblique aponeurosis and transversus abdominis muscle will be bluntly separated to expose the transverse fascia. Dissociation of the hernia sac will be done as described above in the anterior transversalis fascia repair.

Transabdominal preperitoneal or totally extraperitoneal laparoscopic techniques were used to dissociate preperitoneal space, strip spermatic cord peritoneum, anatomise and expose the pubic pore. A polypropylene patch will be placed in the prevesical space and Bogros’ space to achieve repair of the pubic pore-containing area.

### Concomitant treatment

Any medications, with the exception of inguinal hernia-specific treatments, administered during hospitalisation will be recorded. Before starting the trial (ie, at the first visit), detailed information will be recorded regarding concomitant diseases, combined medication and measures to be taken. At discharge, changes in medications and measures to be taken will be recorded. For every combination of medication and measures to be taken, a minimum of the following information will be recorded: drug name (generic preferred), dosage, start date, stop date or continuing use and indications.

### Study flowchart

#### Before surgery

Visit 1 (at admission, day 0)Sign informed consent;Recheck inclusion/exclusion criteria;Demographic data (sex, age, body height, body mass index) and medical insurance type;Type of hernia (indirect or direct);Inguinal hernia classification as type I, II, III or IV according to the adult inguinal hernia and femoral hernia classification (revised in 2003) developed by the Hernia and Abdominal Wall Surgery Group, Society of Surgery, Chinese Medical Association^19^;ASA classification;History of diseases and risk factors* (diabetes mellitus, cardiovascular disease, lung disease, peripheral vascular disease, dementia, hypertension, smoking history and alcohol use history) (*optional evaluation items);Disease onset and admission (interval from first appearance of the lump, main symptoms);Imaging examination (ultrasound, CT);Laboratory examination (routine blood testing, coagulation testing, testing of blood glucose, lipids and electrolytes and hepatic and renal function);Vital signs (body temperature, pulse, respiration rate, blood pressure);VAS pain score;Electrocardiography;Concomitant treatment.

The baseline information of patients with inguinal hernia included in this study is shown in table 2.

**Table 2 T2:** Baseline information of patients with inguinal hernia

Sex	Smoking history
Age	History of alcohol use
Body height	Disease attack and admission
Body mass index	Laboratory examination
Medical insurance type	Imaging examination
Type of hernia	Vital sign
Inguinal hernia classification	VAS pain score
Treatment time	ECG
American Society of Anesthesiologist Classification	Concomitant therapy
History of diseases	
Diabetes mellitus	
Cardiovascular disease	
Lung disease	
Peripheral vascular disease	
Dementia	
Hypertension	

VAS, Visual Analogue Scale.

Predischarge

Visit 2Vital signs (body temperature, pulse, respiration rate, blood pressure);Laboratory examination (routine blood testing, coagulation testing, testing of blood glucose, lipids and electrolytes and hepatic and renal function);Treatment regimen (inguinal hernia-specific treatment).

Surgical approach and patches (type and fixation method); anaesthesia method; drug name (generic preferred), dosage, route, start date, length of drug use will be recorded.Medical costs;Concomitant treatment.

Inguinal hernia-specific treatment, maintenance therapy and drugs used for concomitant treatment.Medical costs because of adverse events (AE).

### Follow-up

Visit 3 (1 week after surgery via clinic visit or telephone follow-up)36-Item Short Form Health Survey (SF-36) score;Medical costs;Hernia recurrence (date and severity of recurrence). Recurrence will be diagnosed by the medical institutions, after being alerted by patients that symptoms are present.Presence or absence of haematoma and/or seroma;Wound infection (date and severity of wound infection).

Visit 4 (1 month after surgery via clinic visit or telephone follow-up)SF-36 score;Medical costs;Hernia recurrence (date and severity of recurrence). Recurrence will be diagnosed by the medical institutions, after being alerted by patients that symptoms are present.Presence or absence of haematoma and/or seroma;Wound infection (date and severity of wound infection).

Visit 5 (3 months after surgery via clinic visit or telephone follow-up)SF-36 score;Medical costs;Hernia recurrence (date and severity of recurrence). Recurrence will be diagnosed by the medical institutions, after being alerted by patients that symptoms are present.Presence or absence of haematoma and/or seroma;Wound infection (date and severity of wound infection).

Visit 6 (1 year after surgery via telephone follow-up)VAS pain score;SF-36 score;Medical costs;Hernia recurrence (date and severity of recurrence). Recurrence will be diagnosed by the medical institutions, after being alerted by patients that symptoms are present;Presence or absence of haematoma and/or seroma;Wound infection (date and severity of wound infection).

Visit 7 (2 years after surgery via telephone follow-up)VAS pain score;SF-36 score;Medical costs;Hernia recurrence (date and severity of recurrence). Recurrence will be diagnosed by the medical institutions, after being alerted by patients that symptoms are present;Presence or absence of haematoma and/or seroma;Wound infection (date and severity of wound infection).

### Outcome measures

#### Primary outcome measure

To reduce the outcome bias of a single evaluation, the incidence of chronic pain at 1 and 2 years after surgery will be evaluated. According to International Association for the Study of Pain, VAS pain score >0 for over 3 successive months indicates chronic inguinal pain.^20^

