### Main objectives

In this study, we will investigate the advantages and disadvantages of the anterior transversalis fascia approach versus the preperitoneal approach for inguinal hernia repair in residents from northern China regarding common postoperative complications (including acute and chronic pain, wound infection, rates of wound infection, haematoma, seroma and hernia recurrence) and severe postoperative complications. These outcomes will provide trial-based evidence for selection of rational therapeutic regimen in the clinic.

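### The primary outcome requires pain lasting more than 3 successive months, but the described schedule has one telephone VAS at 1 year, one at 2 years and no item on duration

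*Protocol article*

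**What the plan says.** Visit numbers here follow the Follow-up section and Table 3; the Study design section numbers the visits differently.

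- **Definition.** Under Primary outcome measure, "the incidence of chronic pain at 1 and 2 years after surgery will be evaluated", and a case is defined by "VAS pain score >0 for over 3 successive months indicates chronic inguinal pain".
- **Schedule.** The Follow-up section lists a VAS at two contacts only: "Visit 6 (1 year after surgery via telephone follow-up)VAS pain score" and "Visit 7 (2 years after surgery via telephone follow-up)VAS pain score". The VAS row of Table 3 is marked at the same two visits and nowhere else.
- **Earlier visits.** The 3-month entry begins "Visit 5 (3 months after surgery via clinic visit or telephone follow-up)SF-36 score;Medical costs;Hernia recurrence" and contains no pain score. The 1-week and 1-month entries are the same in this respect, and the predischarge list under Study flowchart has no pain score either.
- **Conflicting statement.** The text after Figure 1 says that pain is recorded throughout: "Predischarge, and 1 week, 1 and 3 months, 1 and 2 years after surgery: pain, wound infection". It names no instrument, recall period or duration item.
- **Objective.** Main objectives covers "common postoperative complications (including acute and chronic pain, wound infection", so acute pain is an aim as well.
- **Baseline.** Study design, the Visit 1 list and Table 2 all include a preoperative VAS. Table 3 does not mark it.

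**The concern.** The case definition is about duration, while the scheduled measurement is a score at one contact. Two scores 12 months apart do not show whether pain was present for more than 3 successive months around either of them.

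Unless duration is asked about, whoever classifies patients has only the score to go on. With a threshold of anything above zero, discomfort on the day of the call would become chronic pain. If such errors occur at a similar rate in both arms, they add non-cases to both, raise both observed rates and move the risk ratio towards 1. This concerns the trial's only primary outcome, and an analysis plan cannot recover duration data that were never collected.

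**Working it through.** **1. Can the scheduled readings establish the duration?**

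| Source | Postoperative pain readings | Gap before the 1-year reading | Gap before the 2-year reading |
|---|---|---|---|
| Follow-up lists and Table 3 | 1 year, 2 years | no earlier postoperative score | 24 − 12 = 12 months |
| Text after Figure 1, taken at face value | predischarge, 1 week, 1 month, 3 months, 1 year, 2 years | 12 − 3 = 9 months | 12 months |

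On either version, no pair of readings shows more than 3 successive months of pain at the 1- or 2-year evaluation. The SF-36 is collected at Visits 3 to 7 and has a bodily pain scale, but it is a general scale. It is not specific to the groin and is not part of the case definition.

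**2. The plan's own sample size.** Inputs from Sample size: 10% and 3.4%, α = 0.05, power 90%. Assumed because not stated there: two-sided test, 1:1 allocation, pooled variance under the null, no continuity correction.

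n per arm = [z₀.₉₇₅√(2p̄(1−p̄)) + z₀.₉₀√(p₁(1−p₁)+p₂(1−p₂))]² / (p₁−p₂)², with p̄ = 0.067

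This gives 299.5, rounded up to 300 per arm or 600 in total, which is the stated figure. Power at 300 per arm is 90.0%.

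**3. Illustration: one score above 0 counted as chronic pain.** Let u be the share of patients without chronic pain who score above 0 at the call. Every true case is assumed to score above 0. Neither value is in the documents.

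Observed rate = p + (1−p)u

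Power = Φ{ [(q₁−q₂)√300 − 1.96√(2q̄(1−q̄))] / √(q₁(1−q₁)+q₂(1−q₂)) }, where q₁ and q₂ are the observed rates and q̄ is their mean

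| u | Anterior arm | Preperitoneal arm | Risk ratio | Power |
|---|---|---|---|---|
| 0 | 10.0% | 3.4% | 0.34 | 90% |
| 2% | 0.10 + 0.90×0.02 = 11.8% | 0.034 + 0.966×0.02 = 5.3% | 0.45 | 81% |
| 5% | 0.10 + 0.90×0.05 = 14.5% | 0.034 + 0.966×0.05 = 8.2% | 0.57 | 68% |

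The absolute difference shrinks only by the factor (1−u): 6.6 points become 6.6×0.98 = 6.5 and 6.6×0.95 = 6.3. Most of the power loss comes from the larger variance at the higher rates. The effect is clearest on the risk ratio.

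**4. Both readings required.** Assume independent errors and that every true case scores above 0 at both calls. Then u = 5% becomes 0.05² = 0.25%. The rates are 0.10 + 0.90×0.0025 = 10.2% and 0.034 + 0.966×0.0025 = 3.6%, and power is 89%.

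**The case against.** The best defence is that this is a condensed article whose visit lists are not exhaustive. Ischaemic orchitis, painful ejaculation and several other secondary outcomes are to be assessed at every follow-up point, yet none appears in the visit lists. A duration question could therefore exist on the case report form, which is not shown. The definition itself demands duration, and a blinded assessor applying it could ask during the call.

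This stands in part. It rules out saying that duration will not be collected, or that the trial will count a single non-zero score as chronic pain. It does not remove the mismatch, because the article fixes both a duration-based definition and an item-by-item schedule, and the second does not deliver the first.

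The power figures are also open to challenge. They rest on assumed error rates and one reading, whereas the article evaluates two time points expressly to limit bias from a single evaluation. How the two combine is not stated, and requiring both removes nearly all of the loss under the assumptions in step 4. The finding does not depend on these figures.

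A reader might infer three further things that the documents do not support:

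- **That the acute-pain objective has no data.** The text after Figure 1 says pain is recorded at the early visits, and SF-36 bodily pain is collected from 1 week. What is missing is a scheduled pain score.
- **That the 10% and 3.4% rates refer to a different endpoint.** They come from cited reports that are not available here, and the article does not say how those reports measured pain.
- **That a VAS cannot be given by telephone.** The article does not describe its format or administration. The supportable point is that the method should be stated.

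**Conclusion.** The point holds as a mismatch between definition and measurement: from the assessments as described, the more-than-3-successive-months criterion cannot be established at either evaluation. This follows from the text alone.

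The size of the consequence is conditional. If one non-zero score replaced the duration criterion, and 2% to 5% of patients without chronic pain scored above 0, power at 300 per arm would fall from 90% to about 81% to 68%. The risk ratio would move from 0.34 to between 0.45 and 0.57. If both scores had to be positive, power would stay near 89% at the 5% error rate. These figures assume equal error rates in the two arms and full sensitivity; the last also assumes independent errors.

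The point should be fixed because it decides whether the primary outcome can be ascertained, and the remedy is cheap.

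**What to change.** 1. At Visits 6 and 7 (1 and 2 years), add one scripted question: has pain in the operated groin been present for more than 3 successive months (yes/no), and in which month did it start?
2. Define a case as score above 0 plus that duration. Keep the stated requirement that the months be successive; wording that admits recurrent pain would change the primary outcome during the trial.
3. State how the pain score is obtained by telephone. If a different scale is chosen, patients already enrolled with a baseline VAS will not have a matching baseline value.
4. Reconcile the text after Figure 1 and the acute-pain objective with the Study flowchart, the Follow-up lists and Table 3, which list no pain score at Visits 2 to 5. Either schedule the score there or correct the text. Mark the baseline VAS in Table 3.

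**Cost.** One question at calls already planned, an added eCRF item and a protocol amendment. Recruitment began in February 2017 and is ongoing. Any patient whose 1-year call has already taken place will lack the duration item for that call, so the amendment should be made early.

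### The primary outcome needs a VAS above 0 for more than 3 successive months, but the schedule gives single VAS readings at 1 and 2 years and no duration item, so patients with a VAS above 0 cannot be classified

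*Protocol article*

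**What the plan says.** **Definition.** The Primary outcome measure section states that "VAS pain score >0 for over 3 successive months indicates chronic inguinal pain". On timing it says: "To reduce the outcome bias of a single evaluation, the incidence of chronic pain at 1 and 2 years after surgery will be evaluated".

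**Schedule.** In the Follow-up section the VAS appears at two postoperative contacts, both by telephone: "Visit 6 (1 year after surgery via telephone follow-up)VAS pain score;SF-36 score" and "Visit 7 (2 years after surgery via telephone follow-up)VAS pain score;SF-36 score". The 1-week, 1-month and 3-month visits list no VAS; the 3-month entry, for example, opens "Visit 5 (3 months after surgery via clinic visit or telephone follow-up)SF-36 score". The VAS row of Table 3 agrees, with crosses only under Visits 6 and 7. (Table 3 heads Visit 7 as 3 years, the text says 2 years; I use 2 years.) The only other VAS is preoperative. Neither the visit lists nor Table 3 contains a duration question, an onset date for pain, a diary or a repeat call.

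**Text that points the other way.** The Study design text under Figure 1 lists pain among the items recorded at all postoperative visits: "Predischarge, and 1 week, 1 and 3 months, 1 and 2 years after surgery: pain, wound infection". The Abstract likewise places primary outcome assessments at every visit from baseline to 2 years. The text under Figure 1 names no pain instrument, and neither place mentions duration.

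**The concern.** A persistence criterion needs either readings close enough together to show a run or a question about duration. The schedule provides neither. If nothing is added, whoever derives the endpoint must choose a rule for patients with VAS above 0, and the simplest one is to count the score on the day. With the lowest possible threshold, that rule would take in brief discomfort unrelated to chronic pain. It would be a different endpoint from the one defined, and misclassified patients in both arms would bring the two proportions closer together.

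An analysis plan cannot repair this afterwards, because it cannot derive a duration that was never collected. If assessors in nine centres asked without a script, the case rule could differ between centres.

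**Working it through.** **1. Can the scheduled readings show the run?** Set the definition against the schedule.

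| Reading of the schedule | Postoperative readings (months) | Gaps (months) | Shows more than 3 successive months before a contact? |
|---|---|---|---|
| Follow-up lists and Table 3 | 12, 24 | 12 | No |
| Text under Figure 1, if pain were scored at every visit | predischarge, 1 week, then 1, 3, 12, 24 | 2, 9, 12 between the last four | No |

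The last reading before the 1-year contact would be 9 months earlier, and before the 2-year contact 12 months earlier. Positive scores at both ends of such a gap do not show that pain was present in between. A positive score at one end does not show that it lasted 3 months. The broader schedule therefore adds a contradiction without supplying the missing information.

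**2. Who is affected?** VAS 0 at the contact means no run is in progress, so the patient is not in current chronic pain. Only patients with VAS above 0 need duration information. They include every possible case at that contact.

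**3. The plan's own sample size.** Inputs from the Sample size section: p1 = 0.10 (anterior), p2 = 0.034 (preperitoneal), α = 0.05, power 90%, effective n = 600. Two-sided testing and equal arms are my reading. With pooled variance under the null and mean proportion 0.067:

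n per arm = [1.960·√(2·0.067·0.933) + 1.282·√(0.10·0.90 + 0.034·0.966)]² / (0.066)² = (0.693 + 0.449)² / 0.004356 ≈ 299.5, rounded up to 300.

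That gives 600 in total, which reproduces the stated figure.

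**4. Illustration of the day-of-contact rule.** Let f be the share of men without chronic pain who report VAS above 0 at the contact. Assume that f is equal in both arms, that every true case scores above 0, and that 10% and 3.4% are duration-confirmed rates. The documents give no value for f. Then

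q1 = 0.10 + 0.90f and q2 = 0.034 + 0.966f, so q1 − q2 = 0.066(1 − f).

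Worked case, f = 5%: q1 = 0.145, q2 = 0.0823, difference 0.0627, mean 0.11365. Power = Φ[(√300·0.0627 − 1.960·√(2·0.11365·0.88635)) / √(0.145·0.855 + 0.0823·0.9177)] = Φ[(1.086 − 0.880)/0.447] = Φ(0.46) ≈ 68%.

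| f | Anterior | Preperitoneal | Ratio | Power, 300 per arm | Total n for 90% |
|---|---|---|---|---|---|
| 0 | 10.0% | 3.4% | 2.94 | 90% | 600 |
| 2% | 11.8% | 5.3% | 2.21 | 81% | 784 |
| 5% | 14.5% | 8.2% | 1.76 | 68% | 1,074 |
| 10% | 19.0% | 13.1% | 1.45 | 51% | 1,600 |

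The absolute difference shrinks little (6.6 to 6.3 points at f = 5%). Most of the power loss comes from the larger variance at higher event rates. At f = 5%, 0.10/0.145 = 69% of counted cases in the anterior arm and 0.034/0.0823 = 41% in the preperitoneal arm would be true chronic pain.

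**The case against.** The best counter-argument is that this is a journal article. A VAS entry in a schedule is a label, and the question wording and recall window may sit in the full protocol or the eCRF. A blinded assessor is already in contact with the patient and could ask about the preceding months. Part of this stands: the definition could be applied with a recall question, and the absence of one can only be asserted for the text shown. But the article fixes an explicit definition and two concordant, itemised schedules. Those lists go as far as asking for date and severity of recurrence and wound infection, yet give only a score for the primary outcome. That is a mismatch in what is stated, not mere brevity.

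It could also be said that any pain at 1 year is more than 3 months after surgery. That is time since surgery. The definition concerns how long the pain has been present.

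Three stronger readings are tempting, and the documents support none of them:

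- *No patient can be classified.* Patients with VAS 0 can be, and on the planned rates they should be the majority.
- *The plan counts passing pain as chronic pain.* No section says that one VAS above 0 makes a case; the definition excludes it. It is an inference from what the schedule leaves available.
- *The trial will lose power.* The value of f is assumed. The 10% and 3.4% come from cited reports whose pain definition is not given here. If those reports used a single question at follow-up, transient pain may already be in the rates and the dilution shown need not occur.

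**Conclusion.** The point holds in this form: the stated definition and the stated schedule do not fit together, and a patient with VAS above 0 at 1 or 2 years cannot be classified under the definition from the scheduled data. This follows from the text alone and needs no assumption about f. The conflict over whether pain is assessed at every visit or only at 1 and 2 years is also real and must be reconciled, but settling it either way would not show a 3-month run before either contact.

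The size of the consequence is not known. Power of 81%, 68% or 51% against the planned 90% is illustrative and conditional on a day-of-contact rule, on f of 2%, 5% or 10% equal in both arms, and on duration-confirmed planning rates. What can be said firmly is that the primary endpoint's case rule is open for exactly the patients who decide the result. Since recruitment was under way at submission, duration not asked at a contact may not be reliably recoverable later.

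**What to change.** 1. At the 1-year and 2-year contacts, add one fixed item for every patient with VAS above 0: has pain in the operated groin been present for more than the past 3 months (yes/no), with the start date.
2. In the Primary outcome measure section, define a case at each time as VAS above 0 at the contact and pain present for more than 3 successive months by that item.
3. Report VAS above 0 at the contact as a sensitivity analysis.
4. Make the Abstract, the text under Figure 1, the Follow-up lists and Table 3 agree on when pain is assessed and with which instrument.

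The cost is one eCRF question at two contacts that already exist and one sentence in the definition; no visit or patient is added. The item relies on patient recall, and observed rates may be lower than a day-of-contact count. If 10% and 3.4% are duration-confirmed rates, the effective sample size of 600 keeps its basis.
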